### Randomization

For Arms 1 and 2, subjects will be randomized in a 1:1 ratio. 56 opaque sealed envelopes, each containing a study arm, will be randomly picked by a non-team member.

### Study visits and procedures

Informed written consent will be sought from subjects who fulfil criteria for enrolment. All consented subjects will undergo screening, which includes physical examination, full blood count, liver function test, and urinary pregnancy test (for female subjects of child-bearing potential). A flavivirus serostatus screen will also be performed using serum anti-dengue IgG as a surrogate marker for past flavivirus exposure.

**Table 2** shows the detailed study schedule. Study visits will occur on Day 0, 4, 7, 10, 14, 28, 29, 32, 35, 38, 42, 58. Subjects will receive vaccination on Day 0 and Day 28; at these visits blood sampling will be performed prior to vaccination. Subjects will undergo physical examination and research blood sampling at each study visit. Research blood samples will be collected at various time-points (see **Table 2**) for RNAemia measurement, T cell analysis, and antibody titer measurement. Urine samples will also be collected on Days 10, 14, 38 and 42 for urine viral RNA level measurement.

**Table 2 T2:** Study schedule.

	Screening (D-14 to D-1)	D0	D4 (+1d)	D7	D10 (+/- 1d)	D14 (+/- 2d)	D28	D29	D32 (+1d)	D35	D38 (+/- 1d)	D42 (+/- 2d)	D58 (+/- 3d)
**Informed consent**	x												
**Eligibility check**	x	x											
**Medical history and demographics**	x												
**Physical examination**	x	x	x	x	x	x	x	x	x	x	x	x	x
**Vital signs** ^a^	x	x	x	x	x	x	x	x	x	x	x	x	x
**DENV IgG ELISA**	x												
**FBC, Liver panel** ^b^	x												
**Urine pregnancy test** ^c^	x	x					x						
**Randomization** ^e^		x											
**Vaccination**		x					x						
**RNAemia level (NS5 PCR)**		x^d^	x	x	x		x^d^		x	x	x		
**T-cell studies**		x^d^		x	x	x	x^d^		x	x	x	x	x
**PRNT**		x^d^					x^d^						x
**Anti NS1 antibody**		x^d^	x	x	x		x^d^		x	x	x		x
**Urine NS5 PCR**					x	x					x	x	
**Adverse event monitoring**		x	x	x	x	x	x	x	x	x	x	x	x
**Concomitant medication history**		x	x	x	x	x	x	x	x	x	x	x	x

a Vital signs include temperature (oral or tympanic), blood pressure, pulse rate, and respiratory rate.

b FBC includes haemoglobin, red blood cell count, white blood cell count, haematocrit, platelet count, neutrophil, lymphocyte, monocyte, eosinophil, basophil. Liver panel includes total protein, albumin, total bilirubin, alkaline phosphatase, alanine aminotransferase, aspartate aminotransferase.

c For female subjects of child bearing potential only.

d Blood sampling will be performed before vaccine administration on Day 0 and Day 28.

e Only applicable to Arms 1 and 2. Randomization will not be performed for Arm 3. DENV, dengue virus; IgG, immunoglobulin G; ELISA, enzyme linked immunosorbent assay; FBC, full blood count; PCR, polymerase chain reaction; PRNT, plaque reduction neutralization test.

e “x” indicates that the study procedure will be performed.

All subjects will be trained to observe for systemic vaccine-related symptoms (e.g. fever, myalgia, fatigue, headache) post-vaccination. A diary will also be given to the subjects to record such events should they occur during this period. Should they develop systemic symptoms that require intervention, they will report to the study site for medical evaluation and receive the appropriate therapy. Duration of symptoms will be recorded. Any concomitant medication use during this period will also be recorded.

### Study drug administration

As per manufacturer’s instructions, the administered dose of each reconstituted vaccine will be as follows:

1. YF17D (STAMARIL^®^, Sanofi Pasteur): 0.5 mls (4.0 - 5.8 log plaque forming units [PFU]) *via* subcutaneous injection2. JE-YF17D (IMOJEV^®^, Sanofi Pasteur): 0.5 mls (3 - 4 log PFU) *via* subcutaneous injection3. Inactivated JEV (IXIARO^®^, Valneva): 0.5 mls *via* intramuscular injection

In Arms 1 and 2, both JE-YF17D and YF17D vaccines will be administered by subcutaneous injection into the deltoid region of the left/right arm. The second (Day 28) vaccination will be delivered into the ipsilateral arm e.g. if the Day 0 vaccination is administered into the right arm, the Day 28 vaccination will also be administered into the right arm. In Arm 3, inactivated JEV will be administered by intramuscular injection into the deltoid region of the left/right arm and YF17D vaccine will be administered by subcutaneous injection into the deltoid region of the ipsilateral arm.

### Contraception and pregnancy testing

A urine pregnancy test will be performed at screening and on the day of vaccination (Day 0 and Day 28) for female subjects of child-bearing potential. Only those with a negative urine pregnancy test will be considered to be eligible for the study, provided that other eligibility criteria were fulfilled. Both male (if he has a partner of childbearing potential) and female subjects (of childbearing potential) must agree to use adequate and reliable contraceptive measures (e.g. spermicides, condoms, contraceptive pills) or practice abstinence for 10 days after vaccination.

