## Hypothesis and objectives

The overall goal of this study is to define a minimum quantitative threshold of T cells induced by vaccination needed to control subsequent infection, independent of antibodies. We will conduct an experimental study in healthy adult volunteers, leveraging on the immunogenic properties of the licensed live-attenuated yellow fever (YF17D; STAMARIL^®^, Sanofi Pasteur) and chimeric Japanese encephalitis-YF17D (JE-YF17D; IMOJEV^®^, Sanofi Pasteur) vaccines. These vaccines contain the same genomic YF17D backbone (13, 14): vaccination with either vaccine would likely produce T cell responses that, like other flaviviruses, are preferentially directed against the non-structural proteins encoded in their shared genomic backbone, and hence would cross-protect against each other (**Figure 1**). YF17D and JE-YF17D, however, encode different structural pre-membrane (prM) and envelope (E) proteins: vaccination with either would produce neutralizing antibodies protective only against that virus (15). Moreover, YF17D and JE-YF17D vaccination induce different levels of infection as determined by vaccine RNAemia (16, 17), and expectedly differing levels of innate immune responses, allowing us to evaluate how RNAemia and innate immune profile shapes T cell response. The properties of these two live-attenuated vaccines thus provide a unique opportunity to differentiate the role of T cell immunity from humoral immunity in controlling viral infection. In addition, we will also use the licensed inactivated Japanese Encephalitis virus (JEV; IXIARO^®^, Valneva) vaccine to control for the effects of cross-reactive anti-flaviviral antibodies, although we have not observed suppression of YF17D RNAemia from inactivated JEV vaccination (16). Overall, we hypothesize that a high CD4+ and CD8+ T cell response will reduce RNAemia upon challenge with a structurally heterologous virus, and correspondingly result in reduced magnitude of host response to challenge infection. The specific objectives of the study are as follows:

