#### Inclusion criteria

1. Healthy adults, male or female, aged between 21 – 45 years at the time of screening.2. Willingness to comply to study procedures and adhere to study schedule visits.3. Satisfactory baseline medical assessment as assessed by physical examination and a stable health status. The laboratory values must be within the normal range of the assessing site or show abnormalities that are deemed not clinically significant as judged by the investigator. A stable health status is defined as the absence of a health event satisfying the definition of a serious adverse event.4. Accessible vein for blood collection.5. Ability to provide informed consent.6. Female subjects of non-child bearing potential due to surgical sterilization (hysterectomy or bilateral oophorectomy or tubal ligation) or menopause. Post-menopausal subjects must have had at least 12 months of natural amenorrhea.7. Female subjects of child bearing potential with negative urine pregnancy tests on the day of screening and vaccination. Both male (if he has a partner of childbearing potential) and female subjects (of childbearing potential) must agree to use adequate and reliable contraceptive measures (e.g. spermicides, condoms, contraceptive pills) or practice abstinence for 10 days after vaccination.

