#### Exclusion criteria

1. History of presence of cardiovascular, respiratory, hepatic, renal, gastrointestinal, neuropsychiatric, hematological, endocrine or immunosuppressive disorders that would be a risk factor when administered the study vaccines.2. Positive serum anti-dengue IgG by enzyme-linked immunosorbent assay (ELISA).3. Previous receipt of any yellow fever or Japanese encephalitis vaccines (including but not limited those that will be administered in this study).4. Previous history of yellow fever or Japanese encephalitis infection.5. Known allergy to JE-YF17D, YF17D or inactivated JEV vaccines or their components.6. History of severe food/drug/vaccine allergies e.g. angioedema, anaphylaxis.7. Known allergy to egg or egg products.8. History of thymus gland disease.9. Diagnosed with cancer or on treatment for cancer (with the exception of localized basal cell carcinoma) within 3 years prior to screening.10. Evidence of clinically significant anemia (Hb <10 g/dl).11. Blood donation exceeding >450mls in the past 3 months.12. Presence of acute infection in the preceding 7 days or presence of a temperature ≥ 38.0°C (oral or tympanic temperature assessment), or acute symptoms greater than of “mild” severity on the scheduled date of first dose.13. Pregnant or breast feeding women.14. Evidence of substance abuse, or previous substance abuse including alcohol.15. Participation in a study involving administration of an investigational compound (including investigational vaccines) within the past three months, or planned participation during the duration of this study.16. Receipt of anti-inflammatory drugs (such as NSAIDs or systemic steroids) in the past 7 days.17. Receipt of any licensed vaccine in the past 30 days before the first study vaccine dose.18. Any condition that, in the opinion of the investigator, would complicate or compromise the study or wellbeing of the subject.

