### Study design

56 subjects will be randomized into 1 of 2 arms (Arm 1 and Arm 2) in a 1:1 ratio. These two arms will be double-blinded. Subjects in Arm 1 will receive JE-YF17D vaccine (IMOJEV^®^, Sanofi Pasteur) on Day 0, followed by YF17D vaccine (STAMARIL^®^, Sanofi Pasteur) on Day 28. Subjects in Arm 2 will receive YF17D vaccine on Day 0 followed by JE-YF17D vaccine on Day 28. A separate non-randomized non-blinded cohort of 14 subjects will be recruited into Arm 3. Subjects in Arm 3 will receive inactivated JEV vaccine (IXIARO^®^, Valneva) on Day 0 followed by YF17D vaccine on Day 28. **Table 1** summarizes the study design.

**Table 1 T1:** Study design.

Arms	Vaccination schedule	
	1^st^ vaccination (Day 0)	2^nd^ vaccination (Day 28)
Arm 1* (n=28)	JE-YF17D vaccine (IMOJEV^®^, Sanofi Pasteur)	YF17D vaccine (STAMARIL^®^, Sanofi Pasteur)
Arm 2* (n=28)	YF17D vaccine (STAMARIL^®^, Sanofi Pasteur)	JE-YF17D vaccine (IMOJEV^®^, Sanofi Pasteur)
Arm 3** (n=14)	Inactivated JEV vaccine (IXIARO^®^, Valneva)	YF17D vaccine (STAMARIL^®^, Sanofi Pasteur)

*Subjects (n=56) will be randomized in a double-blind manner to either Arms 1 or 2. **A separate cohort (n=14) will be recruited into Arm 3 in a non-randomized, single arm, open label design.

The rationale for these three study arms is as follows: Arm 1 will show the impact of a lower level of RNAemia induced by JE-YF17D vaccination (as compared to YF17D vaccination), and the resultant lower levels of virus-specific CD4+ and CD8+ T cells, would have on YF17D infection. In contrast, YF17D vaccination in Arm 2 would produce higher levels of RNAemia (as compared to JE-YF17D vaccination), and in turn higher levels of virus-specific T cells, thus likely resulting in greater suppression of JE-YF17D infection. The first vaccination in Arms 1 and 2 would provide the RNAemia response in the absence of virus-specific T cells, which would serve as a reference point to interpret the outcome of the second vaccination. For example, the level of suppression of JE-YF17D RNAemia will be the difference in RNAemia levels between subjects who received JE-YF17D as a second vaccination (Arm 2) compared to those who received it as a first vaccination (Arm 1), and similarly for YF17D vaccine. Arm 3 will serve as the control arm, as vaccination with inactivated JE vaccine should not produce any YF17D-specific T cell response.

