### Study discontinuation and withdrawal

Subjects are free to withdraw consent and discontinue their participation at any time without prejudice to them or effect on their medical care. Subjects may be withdrawn, if necessary, to protect their health or the integrity of the study. The investigator also has the right to withdraw participants from the study in the event of inter-current illness, adverse events, treatment failures, protocol violations, administrative, or other reasons. When a subject withdraws from the study, no new data will be collected for study purposes unless the data concern an adverse event related to the study. All details available will be reported and recorded for any subject that withdraws or is removed from the study. Subjects who drop-out or withdraw from the study will not be replaced.

The Principal Investigator (PI) may stop a subject’s participation in the study at any time for one or more of the following reasons: Failure to follow the instructions of the PI and/or study staff, the PI decides that continuing participation could be harmful to the subject, pregnancy, the study is cancelled, and/or other unanticipated circumstances.

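### Contraception is required only for 10 days after vaccination, leaving Days 11–27 uncovered before a Day 28 dose that is live-attenuated in every arm

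*Protocol article*

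**What the plan says.** The protocol article states the contraception rule twice with the same duration, once as inclusion criterion 7 and once under Contraception and pregnancy testing. The persons concerned "must agree to use adequate and reliable contraceptive measures (e.g. spermicides, condoms, contraceptive pills) or practice abstinence for 10 days after vaccination". Neither place mentions the time before a dose, the time between doses, or cover up to the last dose.

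Table 2 puts the two vaccinations on Day 0 and Day 28, and neither day has a visit window. Under Study design, the Day 28 dose is YF17D in Arms 1 and 3 and JE-YF17D in Arm 2; for Arm 1, for example, JE-YF17D is given "on Day 0, followed by YF17D vaccine". Under Hypothesis and objectives both products are described as live-attenuated ("The properties of these two live-attenuated vaccines").

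The article has three other safeguards:

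- **Testing:** "A urine pregnancy test will be performed at screening and on the day of vaccination (Day 0 and Day 28"), with a negative result required by inclusion criterion 7 ("Female subjects of child bearing potential with negative urine pregnancy tests on the day of screening and vaccination").
- **Exclusion:** "Pregnant or breast feeding women" may not enter.
- **Stopping:** the reasons for which the investigator may end participation include "the PI decides that continuing participation could be harmful to the subject, pregnancy, the study is cancelled".

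**The concern.** By excluding pregnant women and requiring contraception after a dose, the protocol treats pregnancy around vaccination as something to avoid. The stated window serves that aim on only one side of the second dose. A conception on Day 29 is guarded against. A conception on Day 25 is not, although that pregnancy would already exist when the live vaccine is given and would continue through all of Days 28–38, the period the rule is meant to protect.

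The testing, exclusion and stopping rules work only on a pregnancy that has been detected. A urine test on the day of the dose cannot rule out a conception in the days just before it. What is at stake is that a participant who follows the protocol exactly is given a live vaccine in early pregnancy.

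**Working it through.** No sample-size or power figure bears on this point. The check is calendar arithmetic on the published schedule.

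**Inputs from the article**

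- Contraception: 10 days after vaccination (inclusion criterion 7; Contraception and pregnancy testing).
- Doses: Day 0 and Day 28 (Study visits and procedures; Table 2).
- Screening: Day −14 to Day −1 (Table 2).
- Day 28 product: YF17D (Arms 1 and 3) or JE-YF17D (Arm 2), so live-attenuated in 3 of 3 arms (Study design; Hypothesis and objectives).
- Urine tests: screening, Day 0, Day 28.

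**Step 1. Days covered, per-dose reading**

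- After the first dose, Days 0–10: 10 − 0 + 1 = 11 days.
- After the second dose, Days 28–38: 38 − 28 + 1 = 11 days.
- Total: 11 + 11 = 22 days.
- Uncovered between doses, Days 11–27: 27 − 11 + 1 = 17 days.

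**Step 2. Other readings**

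- If the 10 days ran only from the last dose, all of Days 0–27 would be uncovered (28 days), which is worse.
- If cover ran without a break from the first dose to Day 38 (39 days), there would be no gap. The text does not say this.

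**Step 3. What the Day 28 test leaves open**

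Let *k* be the number of days from conception to a positive urine test. The documents give no value, so *k* is an assumption. A conception on Day *c* shows on Day 28 only if 28 − *c* ≥ *k*. Conceptions on Days 29 − *k* to 27 are missed, which is *k* − 1 days.

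| Assumed *k* | Days missed | Count | Share of the 17 days |
|---|---|---|---|
| 7 | 22–27 | 6 | 6/17 = 35% |
| 10 | 19–27 | 9 | 9/17 = 53% |
| 14 | 15–27 | 13 | 13/17 = 76% |

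Any lag above one day leaves some of the gap open. These are shares of calendar days, not of the chance of conception.

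**Step 4. Cover under continuous wording**

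- Days 0–38: 39 days.
- With screening on Day −1: 39 + 1 = 40 days, which is 40 − 22 = 18 more than now.
- With screening on Day −14: 39 + 14 = 53 days, which is 53 − 22 = 31 more than now.
- The added days are the 17 between doses plus 1 to 14 before Day 0.

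**The case against.** The strongest reply is that the protocol divides the work: a pregnancy test guards the time before each dose, and contraception guards the time after it. The live Day 0 dose in Arms 1 and 2 is handled the same way, so this looks like a consistent choice rather than a contradiction. The Day 28 test also matters. At a 7-day lag it leaves 6 of the 17 days open, so the 17-day figure alone overstates the exposure. That qualification stands, and the residual window should be quoted beside the gap. The division of work still fails where the test cannot see, in the days immediately before the dose, and using the same arrangement at Day 0 does not repair it.

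A second reply is that this is a condensed article, and the full protocol or consent form may spell out continuous cover. That is possible. But the article has a section on contraception and gives an explicit duration in two places. If continuous cover was intended, the published rule misstates it and needs the same correction.

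Third, the harm cannot be quantified. The article gives no detection lag, no number of women of child-bearing potential and no fetal risk for these vaccines. This is true, and it is why no expected number of exposures is offered. The inconsistency with the protocol's own aim does not depend on those figures.

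**Conclusion.** The concern holds. On the per-dose reading, 17 days (Days 11–27) carry no contraception requirement before a live dose in all three arms, and the only other reading the wording supports leaves more days uncovered. After allowing for the Day 28 test, about 6 to 13 of those days remain open for assumed detection lags of 7 to 14 days. Women who keep using a method through the gap, such as continuing pill users, are not exposed.

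This is a participant-safety defect in a stated rule, and it should be corrected. It has no bearing on sample size, power or analysis. Whether 10 days after a dose is itself long enough cannot be judged from the document and is not questioned here.

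**What to change.** In inclusion criterion 7 and under Contraception and pregnancy testing, give women of child-bearing potential their own sentence: contraception or abstinence is required continuously from screening until at least 10 days after the second vaccination (Day 38). Keep the three urine tests, and leave the duration for men as it is. Because men and women now share one sentence, it has to be split in both places, and the consent wording must match.

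This closes the gap on Days 11–27. Starting at screening also narrows the uncovered time before the live Day 0 dose in Arms 1 and 2. It does not fully close it, since screening may be only one day earlier.

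The cost is a wording change with no added visit, test or analysis. Required cover rises from 22 days to between 40 and 53, depending on the screening date. The longer commitment may put off a few volunteers.

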### Biological specimen analysis

Biological specimens collected at time-points as shown in Table will be analyzed as follows:

#### T cell studies

The quantity of activated/proliferating T cells induced by vaccination will be assessed by measuring the frequency of activated effector CD4+ and CD8+ T cells expressing the activation markers CD38, and HLA-DR. The simultaneous expression of these two markers has been shown to accurately quantify the magnitude of T cell responses induced by live-attenuated viral vaccines (18, 19). Briefly, peripheral blood mononuclear cells (PBMCs) will be stained with a fixable live/dead marker and with antibodies specific to the surface markers CD3, CD4, CD8, HLA-DR and CD38. Stained cells will be fixed and then analysed by flow cytometry, as described previously (18).

The magnitude of YF17D-specific memory T cell responses induced by vaccination will be measured using three complementary methods: 1) Enzyme-linked immunospot assay (ELISpot), 2) Whole-blood cytokine release assay (CRA), and 3) Activation-induced Marker (AIM) assay. For all three assays, pools of 15-mer peptides overlapping by 10 amino-acids that span the C and NS1 to NS5 proteins of YF17D will be used to stimulate either PBMCs or whole blood *ex-vivo.* Overnight (16 hours) stimulation will be performed for the ELISpot assay (PBMCs) and CRA (whole blood), while a 24 hour stimulation will be performed for the AIM assay (PBMCs). ELISpot is a traditional assay which detects T cells that secrete IFN-γ in response to peptide stimulation. The whole-blood CRA measures the level of cytokines (e.g. INF- γ and IL-2) released by T cells in response to peptide stimulation and has shown good correlation with the ELISpot method (20). Finally, the AIM assay will be used to decipher whether the antigen-specific T cell response is sustained preferentially by CD4+ or CD8+ T cells – Briefly, PBMCs collected at various time points will stained with antibodies to the surface markers CD3, CD4, CD8 and activation markers CD134, CD137 and CD139. Stained cells will be fixed and then analysed by flow cytometry, as described previously (21).

#### Vaccine RNAemia

Vaccine RNAemia (as well as urine viral RNA levels) will be measured using RT-qPCR directed against the NS5 gene of YF17D, allowing RNAemia levels induced by JE-YF17D vaccination and YF17D vaccination to be directly compared.

